
##### Refinement of MI-NAV

The purpose of the individual interviews post-release will be to elicit feedback about the MI-NAV intervention, including any strengths and/or limitations perceived by the pilot participants (see Fig. 3 for example questions). The same coding and analysis methods described above will be utilized for the qualitative data collected during this phase of the study. Specifically, we will look for repeating themes from the narratives provided by the first 4–6 pilot participants and make adjustments to the intervention accordingly. This entire process will then be repeated again with another 4–6 pilot participants, leading to a final version of the MI-NAV intervention.

**Fig. 3 Fig3:**
[figure not shown]
Example questions from individual interviews post-release in Phase 2

#### Phase 3: pilot RCT

For the pilot RCT, 80 participants will be recruited and assigned to a condition using a 3:1 ratio, with 60 participants assigned to MI-NAV and 20 participants assigned to SOC. Participants in the SOC condition will also meet with a study interventionist twice while incarcerated. During the first session, SOC participants will receive a pamphlet regarding PrEP during incarceration and will be informed that they can initiate PrEP by speaking with a provider from the correctional facility. Mirroring MI-NAV, the second session will occur 2 weeks before the participant is released from incarceration. This session will involve a referral to community-based PrEP care if the participant is interested and referral to community-based SUD treatment when appropriate. Participants will be randomly assigned to condition using urn randomization; the urn blocking variable will be baseline level of HIV risk behavior as assessed by the HIV Risk Assessment Battery (RAB) [42]. The 3:1 randomization ratio will allow us to maximize the information gained about the MI-NAV intervention while including a comparison condition. RCT participants will complete a baseline interview while incarcerated and follow-up interviews at 1, 3, and 6 months post-release from incarceration. Baseline and follow-up interviews will be conducted by research assistants who will be blind to participants’ assigned condition. RCT participants will receive gift cards in the amount of $25, $30, and $50, respectively, for the 1-, 3-, and 6-month follow-ups (see Table 1 for timing of Phase 3 protocol elements). No compensation will be provided for the baseline interview or sessions/check-ins with the interventionist.

**Table 1 Tab1:** Timing of participant enrollment, receipt of intervention, and assessment activities during Phase 3

Timepoint	Enrollment	Baseline	Post-allocation		
	− t1	0	+ 1 month	+ 3 months	+ 6 months
Enrollment					
Eligibility screen	X				
Informed consent	X				
Allocation		X			
Interventions					
MI-NAV					
SOC		X			
Assessments					
Primary outcomes			X	X	X
Secondary outcomes			X	X	X
Other outcomes		X	X	X	X

##### Measures

The primary outcome for this study is linkage to community-based PrEP care post-release. Secondary outcomes include PrEP initiation during incarceration, PrEP adherence, and retention in PrEP care. HIV and other STI test results will be extracted from medical records, and an HIV test will be performed for research purposes at the 6-month follow-up. Acceptability and feasibility of the intervention will also be assessed. Additional quantitative data will be collected during the baseline and follow-up assessments (see Table 2).

**Table 2 Tab2:** Schedule of assessments

Quantitative measures	Screen	Baseline	1-, 3-, and 6-months follow-up
Inclusion/exclusion criteria (including negative HIV and pregnancy test)	X		
Descriptive information			
Demographics		X	X
PrEP care initiation during incarceration and linkage to care in community			X^a^
PrEP care retention			X^a,b^
PrEP adherence			
Dried blood spot test			X^b^
Self-reported adherence			X
HIV test results		X^a^	X^c^
Other STIs, hepatitis B, hepatitis C test results		X^a^	
Potential moderators of treatment effects			
Timeline followback for alcohol and drug use (TLFB)		X	X
Timeline followback for HIV sex and drug risk behavior and HIV risk assessment battery (RAB)		X	X
Center for Epidemiologic Studies Depression Scale (CES-D)		X	X
Treatment received: treatment services review		X	X
Use of medications/pregnancies		X	X
Intervention acceptability			X^c^
Intervention feasibility			X^c^
Reasons for linkage/non-linkage to PrEP Care/risk reduction			X^c^

^a^Extracted from participants’ medical records

^b^Collected only at 3 and 6 months

^c^Collected only at 6 months

##### PrEP care initiation and linkage to care

Information will be extracted from participants’ medical records at the correctional facility regarding whether PrEP was prescribed and whether PrEP was administered each day during the period of incarceration. Linkage to community-based PrEP care is operationalized as receipt of a prescription for PrEP from a community-based provider within 3 months of release from incarceration, verified through medical record data extraction. This time window was selected because it is consistent with the CDC’s guidelines for PrEP follow-up visits (every 3 months) [38].

##### PrEP adherence and care retention

PrEP adherence will be determined by drug concentrations of emtricitabine/tenofovir in dried blood spot samples collected from participants who have been prescribed PrEP at 3- and 6-month follow-ups. The lower limit of quantification for this test, or ability to detect drug concentrations, is 10 ng/ml [43]. Values under 10 ng/ml will be treated as “undetectable.” Drug concentrations will be entered as continuous variables for data analysis. Self-reported adherence will also be assessed using a well-validated 3-item measure, known simply as the Three-Item Self-Report Measure for Medication Adherence [44]. The three items focus on the past 30 days and include: 1) an assessment of how many doses of medication were missed, 2) a self-rating of how well the participant managed to take their medication in the way they were instructed, and 3) a self-rating of how often the participant managed to take their medication in the way they were instructed. Retention in PrEP care is being defined as attendance to 3-month (± 1 month) clinical appointments in accordance with current CDC guidelines for PrEP care [38]. These guidelines include follow-up visits at least every 3 months to determine if it is clinically appropriate to continue PrEP care. These visits typically involve testing for HIV, bacterial STIs, pregnancy, and assessment of renal function. Attendance to follow-up PrEP appointments will be extracted from participants’ medical records.

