Data analysis will follow a sequence designed to examine the primary outcome questions: (1) Does MI-NAV lead to higher rates of linkage to community-based PrEP care? (2) Does MI-NAV lead to better PrEP adherence, based on dried blood spot tests (DBS), compared to SOC? (3) Does MI-NAV lead to better retention in care compared to SOC? There is little expectation of observed HIV seroconversion, given the modest sample size and 6-month follow-up window. However, seroconversion rates of each condition will be examined. Analyses will also be conducted to examine the relative impact of MI-NAV versus SOC on self-reported PrEP adherence. Following the intention-to-treat principle, all randomized participants will be included in the analyses. We anticipate an attrition rate less than 10%, which will provide us with a final sample size of at least 54 participants in the MI-NAV condition and 18 participants in the SOC condition. This estimate is based on previous research with a high-risk, incarcerated population, in a geographically similar setting, which retained 96% of participants at 12-month follow-up [54]. In addition, we will employ retention strategies that increase retention rates in this population [55], including: (1) offering interview incentives that are higher than normal hourly rates of pay and providing transportation to and from interview locations; (2) conducting regular phone check-ins or sending letters between appointments to ensure contact information has not changed; (3) collecting contact information of secondary contacts, such as friends or relatives, that will know how to reach the participant; and 4) working with local criminal justice agencies, parole officers, and police departments that can help maintain or reestablish contact with participants if necessary.

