Given that this is a pilot study, the primary goal is to yield a stable estimate of the effect size rather than to find statistically significant differences. The effect size estimate will be useful in planning a future RCT. We are aware of the dangers of relying exclusively on small pilot studies to gauge the promise of interventions [56]. These effect size estimates have a large standard error, and we primarily will be hoping to find a pattern of results that is supportive of MI-NAV, at which point a full scale trial will be designed to test for a clinically meaningful effect size. To provide stable odds ratios for estimates of effect size for dichotomous or categorical variables, such as PrEP care linkage, a somewhat larger sample size is required. For continuous variables, group means typically begin to stabilize around 15 participants per group. We believe that the sample size of 60 participants in MI-NAV and 20 participants in SOC, even after attrition, will allow us to evaluate the potential of MI-NAV to improve PrEP linkage while maximizing the number of participants in the MI-NAV condition in order to fully assess the feasibility and acceptability of the intervention.

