#### Primary RCT analyses

Tests of the effects of treatment on the primary outcome variable (linkage to community-based PrEP care) and secondary outcomes (PrEP DBS adherence and retention in care at 3 and 6 months) will be conducted using a fractional logit model [57] estimated by Generalized Estimating Equations (GEE) [58–60]. GEE is a quasi-likelihood estimation method of repeated measures analysis for appropriate modeling of covariance structures when outcomes are correlated across time. Additionally, it allows for the inclusion of both categorical and continuous independent variables. While it is most common to use logistic regression to analyze dichotomous variables, the fractional logit model can be used for any fractional outcome with a range of 0–1. An advantage of GEE over ANOVA is that GEE models nesting by adjusting the standard errors of the test statistics based on the covariances (and variances) of nested observations, rather than depending on calculating differences. These variances and covariances can be modeled based on all data available. Therefore, a subject with missing data for one time point will not contribute to the variance or covariance estimates involving that time point, but their non-missing time points will be used to estimate those variances and covariances.

The primary, between groups, independent variable in the above GEE is treatment group. Variables measured at baseline will be examined using screening runs prior to primary analyses to see which of these baseline measures are most strongly associated with the outcomes (linkage to PrEP, PrEP DBS adherence, retention in PrEP care, and self-reported adherence). Those that show significant relationships with outcome will be entered as covariates in the primary analyses unless there are concerns over multicollinearity. The linear effect of time will also be included as a covariate in these analyses, as we assume that retention and adherence rates will show a tendency to decrease over time. We will also test for non-linear (i.e., linear plus quadratic) effects of time for the repeated measures, adherence and retention. Testing the time by group interaction will indicate the extent to which treatment differences are more or less pronounced over time.

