Analyses will be conducted separately on two overlapping samples. Following the intention-to-treat principle, all randomized participants will be included in the first set of analyses. This is the most conservative approach and represents our main outcome analysis. Analyses will also be conducted on subjects who completed the assigned intervention, the “as-treated” analysis. Although subject to more bias, especially if attrition rates are high, this latter approach answers more directly the question of intervention efficacy by providing an estimate of the maximal effects attained by an intervention. Similar results with both approaches increases confidence in the findings.

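### Dried blood spot adherence is sampled only after a PrEP prescription, which MI-NAV is built to change, yet it is planned as an all-randomized between-arm comparison

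*Protocol article*

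**What the plan says.** Under PrEP adherence and care retention, the article limits DBS to "dried blood spot samples collected from participants who have been prescribed PrEP at 3- and 6-month follow-ups". Values below 10 ng/ml are treated as undetectable, and "Drug concentrations will be entered as continuous variables for data analysis".

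Planned data analysis lists the between-arm question "Does MI-NAV lead to better PrEP adherence, based on dried blood spot tests (DBS), compared to SOC". Primary RCT analyses then tests DBS adherence as a secondary outcome in a fractional logit model fitted by GEE, with treatment group as the main predictor.

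On the analysis set, Planned data analysis states: "Following the intention-to-treat principle, all randomized participants will be included in the analyses". Primary RCT analyses repeats that "all randomized participants will be included in the first set of analyses" and calls this the main outcome analysis.

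On precision, Planned data analysis expects at least 54 MI-NAV and 18 SOC women after attrition and remarks: "For continuous variables, group means typically begin to stabilize around 15 participants per group".

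**The concern.** Whether a woman has a DBS value depends on whether she was prescribed PrEP after randomization. The MI-NAV intervention section sets out to raise prescription both in the facility and in the community, and the primary outcome is itself receipt of a community prescription. If MI-NAV works, the sampled women in the two arms are different kinds of women. Randomization no longer protects a comparison between them. The article also supplies the ingredients for bias: under Potential moderators of treatment effects it cites substance use, risk behavior, housing and depression as related to both poor engagement and poor medication adherence.

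The pilot's stated goal is an effect size for planning a larger trial. An adherence estimate distorted by who got a prescription could mislead that planning in either direction. The same question arises for self-reported adherence.

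**Working it through.** **1. Can the statements hold together?**

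- GEE, as described, uses a participant's non-missing time points. A woman never prescribed PrEP has none, so she drops out and the analysis is not of all randomized women.
- Multiple imputation (Missing data section) is described for missing data in general, and in particular for women with whom contact is lost. Applied here, it would give a drug concentration to women never prescribed the drug, which has no meaning.
- The undetectable rule is written for assayed values. It does not cover women who were never sampled.

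No stated rule brings unprescribed women into the DBS analysis.

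**2. The article's own figure.** With 60 and 20 randomized and 10% attrition, 60 × 0.9 = 54 and 20 × 0.9 = 18. This reproduces.

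**3. How many SOC women give DBS.** The prescription rate is not in the article, so these rates are assumed. Of 18 retained women:

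| Assumed share prescribed | Expected SOC samples |
|---|---|
| 10% | 1.8 |
| 20% | 3.6 |
| 25% | 4.5 |
| 40% | 7.2 |
| 50% | 9.0 |

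At 20%, the binomial probability of 4 or fewer samples is 0.72. Reaching 15 would need 15/18 = 83% prescribed. In MI-NAV, 30% to 70% prescribed gives about 16 to 38 of 54.

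**4. Size and sign of the selection effect.** All inputs here are assumed. Let pS and pM be the shares prescribed in SOC and MI-NAV. Let mA be mean adherence (0 to 1 scale) in women prescribed under either arm, mI that of women prescribed only because of MI-NAV, and d the true adherence gain in the first group. Assume every woman prescribed under SOC would also be prescribed under MI-NAV.

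- Among prescribed women, the SOC mean is mA and the MI-NAV mean is [pS(mA + d) + (pM − pS)mI]/pM. The difference is [pS·d − (pM − pS)(mA − mI)]/pM.
- In all randomized women, with no prescription scored 0, the difference is pS·d + (pM − pS)mI.

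| pS | pM | mA | mI | d | Prescribed only | All randomized |
|---|---|---|---|---|---|---|
| 0.20 | 0.50 | 0.70 | 0.50 | 0 | −0.12 | +0.15 |
| 0.20 | 0.50 | 0.70 | 0.50 | 0.10 | −0.08 | +0.17 |
| 0.40 | 0.50 | 0.70 | 0.30 | 0.10 | 0.00 | +0.07 |
| 0.20 | 0.50 | 0.70 | 0.70 | 0 | 0.00 | +0.21 |
| 0.20 | 0.50 | 0.50 | 0.70 | 0 | +0.12 | +0.21 |

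Row 1 worked: −(0.30 × 0.20)/0.50 = −0.12, and 0.30 × 0.50 = +0.15. Row 2 turns a real gain negative and row 3 hides one. Row 4 has no bias. Row 5 creates a gain that does not exist.

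With d = 0, pS from 0.1 to 0.4, pM from 0.3 to 0.7, mA = 0.70 and mI from 0.3 to 0.5, the prescribed-only difference runs from −0.04 to −0.34. With mA = 0.5 and mI = 0.7 it runs from +0.04 to +0.17.

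**5. A gentler model.** A simulation linked engagement and adherence by a correlation, with 20% versus 50% prescribed and no effect on adherence once prescribed. The prescribed-only difference was 0 at correlation 0, −0.04 at 0.3 and −0.06 at 0.5. The all-randomized difference was +0.15 to +0.16.

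**The case against.** The best reply is that the article restricts blood collection, not the analysis set. The set is declared to be all randomized women, and the two statements fit if unprescribed women are scored zero or undetectable. A full protocol or analysis plan might say so. This stands in part: the sampling rule is not itself an error, and a prescribed-only comparison is one consequence of the text, not something the article announces. But the methods the article does name, GEE on available data and multiple imputation, do not produce that scoring. They lead to a subset contrast or to a meaningless imputation.

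Several stronger readings are tempting and are not supported:

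- *The bias runs against MI-NAV.* A reader might infer this from the idea that SOC women who obtain PrEP are the self-motivated ones. SOC women also have two interventionist sessions, a pamphlet and a referral. Women brought in by MI-NAV might adhere as well or better, particularly as monthly check-ins address adherence. The direction cannot be read from the documents.
- *The comparison is confounded.* The accurate term is selection on a post-randomization variable.
- *The plan breaks its own rule of 15 per group.* That sentence is a general remark about means, not a commitment for DBS. It is a point of precision, separate from bias.
- *Only women linked in the community are sampled.* The text says prescribed, without saying where, so facility prescriptions may enlarge the sampled group.

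It is also fair that an all-randomized detectability outcome does not isolate adherence. In rows 1, 4 and 5 its whole difference comes from the additional women prescribed PrEP.

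**Conclusion.** The concern holds as an internal conflict: a measurement conditional on a post-randomization event that the intervention targets is presented as an all-randomized comparison, with no rule to bridge the two. The bias can hide, reverse or inflate an adherence effect, and it vanishes if women prescribed because of MI-NAV adhere like the others. The sizes shown, from −0.34 to +0.17 with no true effect on adherence, rest wholly on assumed prescription and adherence rates. The small SOC count is likely to matter but also depends on an assumed rate.

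This should be fixed, but it is not a threat to the trial's main result. DBS adherence is classed as secondary, linkage is unaffected, and the article already warns of large standard errors.

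**What to change.** - Define the between-arm intention-to-treat DBS outcome in all randomized women as drug detectable (at least 10 ng/ml), yes or no, at 3 and at 6 months.
- Count women with no PrEP prescription as not detectable, and state whether facility prescriptions, community prescriptions or both count.
- Leave missed draws in prescribed women to the missing-data plan.
- State that this outcome measures uptake and adherence combined and overlaps with linkage.
- Report concentrations and self-reported adherence among prescribed women by arm, with the number sampled, as descriptive and non-randomized, without a causal between-arm adherence claim.

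A 0/1 outcome also suits the fractional logit model, which the article describes for outcomes between 0 and 1; a raw concentration does not lie in that range.

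The cost is a change of estimand and scale, with no new samples. Adherence given a prescription would no longer be tested between arms, and the continuous concentration would survive only in the descriptive table.

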##### Potential moderators of treatment effects

It is possible that certain variables may be potential moderators of treatment effects. Alcohol and drug use [24–26], HIV risk behaviors [45, 46], housing status [47, 48], and depressive symptoms [27] have been found to be associated with poor treatment engagement and medication adherence in previous research. Therefore, we will be collecting information about these variables for exploratory analyses. The Timeline Follow Back (TLFB), a calendar-assisted structured interview, will be used to collect data on the number of standard drinks consumed per day and types of drug classes used each day within a given time period [49–51]. The TLFB will also be used to assess daily HIV drug and sex risk behaviors. In addition, the HIV Risk Assessment Battery (RAB) will serve as a measure of overall HIV sex and drug risk behavior [42]. The RAB assesses the frequency of behaviors such as injection drug use, sex without a condom, sex while under the influence of substances, and sex in exchange for money or drugs. Frequencies fall on scales with response options between a range of 0 (least frequent option, depending on behavior) to 3 (most frequent option, depending on behavior). An overall risk score, which is correlated with seroconversion, is computed by adding the values corresponding with the response option (e.g. 0–3) and then dividing this total score by the highest possible score. Information on housing status will be collected, along with other demographic information, at baseline and each of the follow-up appointments. Finally, the Center for Epidemiologic Studies Depression Scale (CES-D) will be used to measure level of depressive symptoms [52].

##### Intervention feasibility and acceptability

At the conclusion of the study, we will compile a patient eligibility rate, enrollment refusal rate, rate of recruitment, and follow-up completion rate in order to evaluate the feasibility of conducting a subsequent larger scale study using this protocol. We will also compile a study dropout rate and intervention session completion rate, as indices of acceptability. In addition, the 8-item Client Satisfaction Questionnaire-Revised will be used to further evaluate intervention acceptability and feasibility [53].

##### Reasons for PrEP care linkage and non-linkage/risk reduction strategies

During the 6-month follow-up assessment, all participants will complete a brief qualitative interview in which they will be asked to reflect on factors that impacted their use or non-use of PrEP both while incarcerated and after release. Participants will also be asked about any other HIV risk reduction strategies that were employed. During analysis, participants’ responses will be stratified and examined based on level of PrEP uptake per condition.

